### 3.6. Data Analysis

#### 3.6.1. Sample Size Calculation

Estimation of the needed sample size was based on the result of the preliminary study. The primary outcome of the study is patient self-reported symptoms scores on a 7-point Likert scale. The mean difference between the symptoms scores of the two groups of the preliminary study was 0.47, with the standard deviation (SD) being 0.53. The basis for estimating the required sample size is that it has at least 80% power (*β* = 0.20) to detect the mean difference of 0.47 points, with significance testing at the *α* = 0.05 level and SD = 0.53; using a two-sided test, the ratio of the two groups is 1 : 1, with three cross-overs, assuming no period effect or treatment × time interaction, under the given model parameters [28, 29]. The sample size was calculated by using PASS 11.0 software (NCSS LLC, Kaysville, UT, USA). Preliminary calculations concluded that 21 patients would be needed to meet the requirements. Taking into account the high drop-out rates of N-of-1 trials (30%), the final sample size was determined to be 30.

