## 2. Hypothesis

The efficacy of TCM based on syndrome differentiation treatment is expected to be significantly better than that of placebo at both the individual and population levels in N-of-1 trials. But there is the possibility of invalid cases, which may be related to some factors (such as the severity of the disease, bacterial strains, and accompanying disease). Introducing carryover effect of TCM as confounding variables into hierarchical Bayesian statistics, and using the “borrowing from strength” [16, 17] function of prior information, can improve the reliability and sensitivity of N-of-1 trials of TCM.

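### The figure of 21 patients for 80% power does not follow from the stated inputs under three within-patient pairs; it matches the per-group size of an unpaired two-sample t-test

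*Protocol article*

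**What the plan says.** Section 3.6.1 bases the size on a preliminary study whose between-treatment difference in symptom score "was 0.47, with the standard deviation (SD) being 0.53". The target is that "it has at least 80% power" "to detect the mean difference of 0.47 points", "with significance testing at the *α* = 0.05 level and SD = 0.53". The design is given as "using a two-sided test, the ratio of the two groups is 1 : 1, with three cross-overs", with period effects and treatment-by-time interaction assumed absent. PASS 11.0 is named as the software, but not the procedure used. The result is: "Preliminary calculations concluded that 21 patients would be needed to meet the requirements". A 30% drop-out allowance raises this to 30.

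Section 3.1 describes a different structure from two groups: every patient goes through three pairs of periods, and each pair contains one active and one placebo period in random order. Section 3.6.1 does not say whether 0.53 is the SD of scores, of one pair's difference or of patient-mean differences. It gives no within-patient correlation and no treatment-by-patient variance.

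**The concern.** A design in which each patient supplies three paired comparisons should need far fewer patients than an unpaired comparison with the same difference and SD. A result of 21, together with a 1:1 ratio of two groups, looks like the output of a parallel-group procedure.

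If so, the stated power is not the power of the trial being run. A reader cannot tell what difference 21 completers can detect. This matters more here than in most trials, because the stated aim is to raise the sensitivity of N-of-1 trials and to compare a hierarchical Bayesian analysis with the paired t-test and meta-analysis. Someone who believes the conventional population-level comparison has 80% power will misjudge how much room is left for improvement if the figure is really nearer 97%.

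**Working it through.** **Inputs (section 3.6.1).** Difference d = 0.47; SD s = 0.53; two-sided α = 0.05; target power 80%; 21 evaluable patients; drop-out 30%. From section 3.1: k = 3 pairs per patient. All powers use the noncentral t distribution.

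**Step 1: reproduce the 21.** For an unpaired two-sample t-test with n per group, the noncentrality is d / (s√(2/n)) on 2n − 2 degrees of freedom.
- n = 20: 0.47 / (0.53 × √0.1) = 2.80, power 78.0%.
- n = 21: 0.47 / (0.53 × √(2/21)) = 2.87, power 80.07%.

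So 21 is the smallest per-group size, which would mean 42 patients in a parallel trial. The drop-out step is correct: 21 / 0.7 = 30.

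**Step 2: three pairs per patient.** Test the patient-mean differences with a one-sample t-test: noncentrality d√n / S on n − 1 degrees of freedom, where S is the SD of patient-mean differences. S depends on what 0.53 is.

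| Meaning of 0.53 | S | Patients for 80% | Power at 21 |
|---|---|---|---|
| SD of patient-mean differences | 0.53 | 13 (83.5%; 12 give 79.8%) | 97.1% |
| Per-period within-patient SD, no effect heterogeneity | 0.53 × √(2/3) = 0.433 | 9 (81.4%) | 99.7% |
| SD of one pair's difference, no effect heterogeneity | 0.53 / √3 = 0.306 | 6 (84.9%) | over 99.9% |

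Under the first reading, the difference that 21 patients detect with 80% power is about 0.34, not 0.47.

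**Step 3: nearest crossover variant.** With a single pair, 0.53 as the per-period SD and zero correlation, S = 0.53 × √2 = 0.750. This needs 22 patients, and 21 give 78.0%. It misses the stated target and uses only one of the three cycles.

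**Step 4: what would bring 80% back at 21?** Solving for 80% power at n = 21 gives S of about 0.73. If patients differ in their true treatment effect with SD τ, then under the per-period reading S² = τ² + 2s²/3. Here 2s²/3 = 2 × 0.2809 / 3 = 0.187, so τ = √(0.73² − 0.187) ≈ 0.59.

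| Assumed τ | S | Power at 21 |
|---|---|---|
| 0 | 0.433 | 99.7% |
| 0.3 | 0.527 | 97.3% |
| 0.5 | 0.661 | 87.2% |
| 0.6 | 0.740 | 79.1% |

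If 0.53 is instead one pair's difference, the τ required is √(0.73² − 0.2809/3) ≈ 0.66. If 0.53 is already the SD of patient-mean differences, it contains τ and nothing should be added. The τ values are assumptions, since the article gives none.

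**The case against.** **The procedure is inferred.** The article names no PASS procedure and cites sources for its model that are not available here. An exact match is strong evidence but not proof that an unpaired test was run. This stands, and it is why the point says the figure appears to come from that test. The mismatch with three pairs does not depend on the inference.

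**Effect heterogeneity could rescue the number.** Section 2 expects some patients not to respond, and section 3.6.2 plans individual effects and responder classification, so treatment-by-patient variation is plausible. This also stands: one cannot say that no three-pair calculation gives 80% at 21. But the required SD, about 0.6, exceeds the 0.47 effect itself and is nowhere stated. The narrower claim, that the stated inputs do not yield 21, is untouched.

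**The assumption of no period effect.** A reader might set "with three cross-overs, assuming no period effect" against the hypothesis in section 2, "Introducing carryover effect of TCM as confounding variables into hierarchical Bayesian statistics", and call it a contradiction. The documents do not support that. It is an openly declared sizing assumption, outcomes are measured in the last week of each period to limit carryover, and section 3.6.2 plans to examine carryover, period effects and autocorrelation. A simpler model for sizing than for analysis is common practice.

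**A condensed article.** A fuller protocol may define the SD. That would excuse an omission, but not a stated result that disagrees with its own stated inputs and design.

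**The key analysis is Bayesian.** With prior information from earlier trials, any frequentist power is only a guide. That is fair, but the article itself chose to justify its size by frequentist power.

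**Conclusion.** The point holds, with moderate severity. The stated inputs combined with three within-patient pairs need 6 to 13 patients rather than 21, and give at least 97% power at 21 rather than about 80%. These figures rest on a t-test of patient-mean differences, no adjustment for carryover, and either no effect heterogeneity or heterogeneity already contained in 0.53.

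Three stronger readings are tempting and not supported:
- **That 42 patients are needed and the trial is too small.** The per-group 21 belongs to a parallel design, whereas here every patient receives both treatments. On the stated inputs the error is conservative.
- **That the true power is 97%.** This is one reading of an unlabelled SD. It falls to about 79% if 0.53 is the per-period SD and the treatment-by-patient SD is 0.6. A carryover term would also cost precision, by an amount that depends on the sequences and on a carryover model the article does not specify.
- **That enrolment could be cut, or is now proven sufficient.** Neither can be settled until the variance components are known.

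**What to change.** In section 3.6.1, state which SD 0.53 is: of scores, of one pair's difference, or of patient-mean differences in the preliminary study. Replace the sentence giving 21 with a paired three-pair calculation that names the procedure and states the within-patient and treatment-by-patient variance components. For 21 completers, report power for 0.47 and the difference detectable with 80% power over a range of treatment-by-patient SD, for example 0 to 0.6. Add a carryover-adjusted version as a sensitivity calculation, with its sequences and carryover model stated. Do not print a single replacement power until the SD has been identified from the preliminary data.

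The cost is one rewritten paragraph and a short calculation, plus a look back at the preliminary data for the variance components. The point asks for no change to the enrolment target of 30.

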#### 3.6.2. Statistical Analysis

To avoid or decrease the potential carryover effect of the previously used drug, the values of the outcomes will be measured in the last week of each observation period. All patients with at least one complete treatment cycle will be included in the analysis. The data generated in this study will constitute a dataset, and the database will be established by experts specializing in statistical analysis of N-of-1 trials. For all data in this dataset, carryover effect, period effects, and autocorrelation will be carried out and analyzed by statistical experts [4, 10].

Hierarchical Bayesian statistical method will be the key statistical method of this study. It is based on the Monte Carlo technology of Markov's Bayesian hierarchical model calculation chain and uses WinBUGS software for calculation. The advantages of a Bayesian approach over normal frequentist statistical methods are discussed in detail in Zucker et al., Schluter and Ware, and Nikles et al. [30–32]. We intend to use the advantages of Bayesian analysis: (1) various levels and confounding variables can be introduced, such as the potential carryover effect of TCM, the severity of bronchiectasis, sputum culture (whether *Pseudomonas aeruginosa* is positive), and TCM syndrome differentiation (lung and spleen deficiency syndrome, qi and yin deficiency syndrome, phlegm-heat syndrome (mild, moderate, severe, etc.)), and the difference in efficacy under stratification and confounding variables can be analyzed. Using the data of similar N-of-1 trials that have been completed in the past as prior information, from the Bayesian analysis we will obtain posterior distributions for the mean treatment effect at the population level, as well as posterior distributions for the treatment effects at the individual level, that will exhibit borrowed strength from the population estimates through shrinkage to the population mean. The probability distributions of each model will be evaluated to assess violations and data transformations undertaken, where necessary. Conventional burn-in periods, model convergence and stability diagnostics, and residual checks will be employed.

The forms of hierarchical Bayesian statistics analysis results will be as follows: (1) the mean of the posterior distribution of the mean difference between the outcomes of placebo and the test drug, which gives the best estimate of the difference in the overall effect size between the treatments; (2) the relevant 95% credible region, which gives uncertainty interval of the posterior distribution (2.5 and 97.5 percentiles in this case), and (3) the posterior probability of mean difference that the test drug will be better than the control drug, which describes the likelihood that the patients will tend to actively treat in future cycles. When these estimated values exceed predetermined threshold values (for example, the improvement of the average of the total points of all symptoms is ≥0.5 points), the patient will be defined as a “responder” [33, 34].

To compare the novel methodology of aggregated N-of-1 trials with the traditional analysis methods, the Bayesian method will be compared with other common statistical methods used in N-of-1 trials (including paired *t*-test and meta-analysis) to evaluate its sensitivity and applicability to N-of-1 trials of TCM.

## 4. Discussion

Our previous studies [10] showed that N-of-1 trials could reflect the individualized characteristics of traditional Chinese medicine (TCM) syndrome differentiation with good feasibility and compliance, but the sensitivity was low. We supposed that the improvement of statistical models may be beneficial in establishing a clinical efficacy evaluation method that meets the characteristics of TCM.

For the past few years, hierarchical Bayesian statistical method has been widely used in this field. Senior et al. [14] concluded that the advantages of Bayesian method over ordinary frequentist statistical methods, such as the following: (1) both individual and aggregate analyses are simultaneously and coherently undertaken, (2) natural hierarchies and serial correlations within the study can be exploited and accommodated (such as clustering by physician, setting, or location), (3) confounding variables can easily be introduced into Bayesian model, and (4) they naturally allow incorporating any relevant trial information that may be sourced from elsewhere [14]. In addition, Bayesian methods allow for the use of prior available information (e.g., previous trial results) within the analysis. In the hierarchical Bayesian model, previous data and new trial data belong to a continuous data chain. When new trial data are generated, the data chain is updated to generate more accurate posterior information [15].

Bayesian methods as yet have not been used in N-of-1 trials of TCM. In this trial design, we consider introducing the carryover effect of TCM as confounding variables into hierarchical Bayesian statistics [12, 13] and using the data of similar N-of-1 trials that have been completed in the past as prior information, without increasing the cycles of the trials, by “borrowing from strength” from the results of other similar N-of-1 trials to improve the reliability and sensitivity N-of-1 trials of TCM. In addition, the Bayesian method will be compared with other common statistical methods used in N-of-1 trials (including paired *t*-test and meta-analysis) to evaluate its sensitivity and applicability to N-of-1 trials of TCM.

It should be mentioned that this trial protocol has other characteristics: (1) a relatively reasonable observation and washout period were determined through the run-in period combined with investigators' clinical experience [10, 18]; (2) placebo control used in the study has high test sensitivity, can detect the absolute effectiveness and safety of the test drug, and has a high ability to reduce bias; the carryover effect of TCM can also be calculated from it; (3) highly individualized treatment based on syndrome differentiation: not only can the investigational drug be individualized, but it can also be adjusted according to the patient's condition and syndrome changes during the whole process of N-of-1 trials, which conforms to the principle of “do what is proper according to the circumstances” in TCM. Meanwhile, the control drug will be always unchanged. Our ultimate goal is to explore the establishment of an objective evaluation method of therapeutic effects reflecting the essence of TCM treatment based on syndrome differentiation in line with the trend of international medical development. In a broad sense, it may have reference value for clinical trials of TCM for other chronic diseases.

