## 3. Methods

### 3.1. Study Design

These are a series of randomized, double-blind, placebo-controlled, N-of-1 clinical trials. According to our previous experimental design [10, 18], the brief description is as follows: we will conduct a 4- to 8-week run-in period for patients who meet the inclusion criteria to obtain onset time after drug administration and efficacy maintenance time after drug withdrawal (with the changes of patients' self-rated symptom scores as the primary outcome), so as to determine the length of observation period and the estimation of washout period. Combining the results in the run-in periods and the previous results [10, 18], we fixed the observation periods of the N-of-1 trials to four weeks. Three cycles (pairs) of N-of-1 trials will be conducted in the same individual, with each cycle consisting of two observation periods (the experimental period and the control period) assigned in random order [18, 19]. The medications will be taken for three weeks and then stopped for one week in each observation period. We will measure the outcomes in the last week of each period and the time before this is supposed to be the washout period (Figure 1). The changes in patients, self-rated symptom scores are the primary outcome (the 7-point Likert scale). Hierarchical Bayesian statistical method will be the key statistical method of this study. Different mathematical models (paired *t*-test, hierarchical Bayesian, and meta-analysis) for N-of-1 trials of TCM will be compared to improve the sensitivity and applicability of N-of-1 trials of TCM on both individual and population levels. The trial was performed at the clinic of Yueyang Hospital of Integrated Traditional Chinese and Western Medicine, Shanghai University of Traditional Chinese Medicine. This study started in January 2019 and was expected to end in December 2022.

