#### 3.3.2. Treatment of TCM

*Syndrome Differentiation Treatment*. The treatment based on syndrome differentiation will be conducted by chief physicians. To ensure the high quality of treatment based on syndrome differentiation, if there is any difficulty or dispute, a third party (distinguished veteran doctor of TCM) will be invited to provide consultation and guidance. It is the highly individualized treatment of TCM, the modification of Bronchiectasis Stabilization Decoction [9] (Rhizoma Fagopyri Cymosi 30 g, Radix Lithospermi 15 g, Radix Ophiopogonis 15 g, Poria 15 g, Radix Astragali 20 g, Rhizoma Bletillae 10 g, Platycodon grandiflorum 10 g, and Semen Coicis 30 g) based on syndrome differentiation. For example, for patients with lung and spleen qi deficiency syndrome, we will add Radix Codonopsis Pilosulae, Pericarpium Citri Reticulatae, and Atractylodes Macrocephala Koidz; for patients with qi and yin deficiency syndrome, we will add Radix Adenophorae, Radix Glehniae, and Radix Rehmanniae; for patients with obvious phlegm-heat syndrome, we will add Radix Scutellariae and Herba Violae. In addition, we can also adjust the individualized decoction according to the patient's other symptoms such as loss of appetite, insomnia, and constipation. In order to reflect the high flexibility of TCM, the prescription based on syndrome differentiation can be adjusted appropriately in accordance with the patient's condition changes throughout the entire study duration. The drug (in the form of TCM granules) which has passed quality inspection in line with the national norms [18] will be provided by the Sichuan New Green Pharmaceutical Technology Development Co., Ltd.
*Placebo*. Placebo is made by dextrin, bitter agent, edible pigment, etc., and adding 5% of the test drug. There will be no difference between the placebo and the test drug in terms of dosage form, appearance, color, specification, label, and so forth [24]. The individualized decoction and placebo will be used in the same way: take one decoction a day in two doses.

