### 3.4. Randomization and Blinding

According to our previous experimental design [10, 18], the brief description is as follows: a specialized pharmacist will use a computer (software SPSS 15.0) to generate random numbers and random number sequences to determine the order of medication for each subject in each observation period, such as BA-AB-BA or AB-BA-BA. The pharmacist will use the method of flipping a coin to determine which of A or B represents individualized prescription or control prescription, record the blind code, and keep it properly. After evaluating the patient's TCM syndromes, the doctor will prescribe both individualized prescription and control prescription. Then, the two prescriptions will be delivered to the specialized pharmacist by the TCM Pharmacy. Then, the pharmacist will prepare the drug following the randomized medication order and the blind code.

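### The individualized prescription may be adjusted throughout while the control never changes, which conflicts with the placebo-matching promise and puts the blinding of a self-rated primary outcome at risk

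*Protocol article*

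**What the plan says.** Section 3.1 describes the design: "These are a series of randomized, double-blind, placebo-controlled, N-of-1 clinical trials". Three cycles of two periods are run in each patient, and section 3.4 has a pharmacist generate random sequences "to determine the order of medication for each subject in each observation period, such as BA-AB-BA or AB-BA-BA".

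On the active product, section 3.3.2 states that "the prescription based on syndrome differentiation can be adjusted appropriately in accordance with the patient's condition changes throughout the entire study duration". The Discussion presents this as a feature of the design: "it can also be adjusted according to the patient's condition and syndrome changes during the whole process of N-of-1 trials".

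On the control, section 3.3.2 gives the composition, "Placebo is made by dextrin, bitter agent, edible pigment, etc., and adding 5% of the test drug", and the matching standard: "There will be no difference between the placebo and the test drug in terms of dosage form, appearance, color, specification, label, and so forth". The Discussion then adds: "Meanwhile, the control drug will be always unchanged".

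In section 3.4 the doctor prescribes both products after evaluating the syndrome, and the pharmacist prepares them according to the sequence and blind code. The primary outcome in section 3.5.1 is the patient's own diary rating on a 7-point scale.

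**The concern.** The matching standard ties the placebo to the test drug, but the Discussion fixes the placebo while the test drug may move. Both statements can be kept only in a patient whose prescription is never modified. In any other patient, following the Discussion sentence means giving a placebo built on a formula no longer in use.

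This design is more exposed than a parallel-group trial because every patient takes both products repeatedly and can compare them. The modifications may be substantial: section 3.3.2 gives examples in which two or three herbs are added for a syndrome, with further changes for appetite, sleep or bowel symptoms. If a difference is noticed, expectation can enter the self-rated score directly. It would coincide with treatment, so neither the hierarchical Bayesian model nor the paired t-test could separate it from efficacy. Section 3.6.2 also classifies individual patients as responders, so a single patient's conclusion is exposed as well as the population mean.

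**Working it through.** No figure in the plan depends on this point, so the check is mainly a comparison of statements.

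**Step 1. Before any modification.** Call the first formula F1. The active product is F1. The placebo is excipients plus 5% of F1, matched to F1. Sections 3.3.2 and 4 agree.

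**Step 2. After a modification to F2.** The active product is F2.
- Under section 3.3.2 the placebo should hold 5% of F2 and not differ from F2 in the listed respects.
- Under section 4 the placebo still holds 5% of F1, with pigment and bitter agent set against F1.

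The two rules give different products. Section 3.4, as written, does not settle which applies: it has both products prescribed after the syndrome evaluation and does not say whether that step is repeated after an adjustment.

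**Step 3. What the patient can compare.** 3 cycles × 2 periods = 6 periods, 3 on each product. If a modification takes effect between cycles 1 and 2, cycles 2 and 3 compare F2 with a placebo built on F1. Any perceptible change shows only in the active periods.

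**Step 4. Can the bias be sized?** Let *p* be the share of patients who have an adjustment and notice it, and *s* the resulting shift in the within-patient treatment difference. The average bias is then *p* × *s*. The article gives neither quantity. *p* cannot exceed the share of patients who are adjusted, which is also not given. It is zero if no one is adjusted or no change is perceptible. No estimate follows.

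**Step 5. A scale only, on assumed values.** The benchmarks are the planned difference of 0.47 (section 3.6.1) and the clinically important difference of 0.5 (section 3.5.1). The last column further assumes no true effect, 21 patients, a two-sided paired t-test at 0.05, and 0.53 as the SD of within-patient differences. The article does not say that 0.53 is that SD; a larger one would lower these probabilities. The noncentrality is bias ÷ 0.53 × √21, on 20 degrees of freedom.

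| Assumed average bias | ÷ 0.5 | ÷ 0.47 | Noncentrality | Probability of a significant result |
|---|---|---|---|---|
| 0 | 0% | 0% | 0 | 0.05 |
| 0.1 | 20% | 21% | 0.86 | 0.13 |
| 0.2 | 40% | 43% | 1.73 | 0.38 |
| 0.3 | 60% | 64% | 2.59 | 0.69 |

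The table shows how sensitive the result would be to a bias of a given size. It does not say that such a bias would occur.

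**The case against.** The strongest reply is that the sentence stands in the Discussion, in a list of design features, and may mean only that the comparator is a placebo throughout. The Methods lean towards matching: the placebo is defined from the test drug, and the doctor prescribes both products. The article also says it describes the randomization and blinding procedure briefly, following an earlier design. This reading is possible, but the sentence does not say it. It sets an unchanging control directly against an adjustable active drug. If the milder meaning was intended, correcting one sentence settles the matter.

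A reader might go further and infer that blinding has failed. The documents do not support that:
- No passage shows that an adjusted formula differs perceptibly. Both products are granules, the placebo carries pigment and a bitter agent, and the matching list does not name taste or smell. Some changes may go unnoticed.
- That granules which change must be active follows only if the patient knows the placebo is fixed. Nothing says patients are told.
- That the physician learns the allocation requires seeing or hearing about the dispensed granules. The pharmacist prepares them and holds the code.
- That the bias would always favour the active product is plausible as a tendency, but not established.

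These points limit the claim to a risk. They do not remove the conflict between the two statements about the placebo.

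**Conclusion.** The point holds as a contradiction between stated rules, with a risk to blinding as its consequence. An always-unchanged control cannot be relied on to meet section 3.3.2's composition and matching standard after the test drug is modified. The double-blind claim and the self-rated primary outcome are therefore exposed to expectation bias in patients whose prescription is adjusted. Patients who are never adjusted are unaffected.

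The size of the bias cannot be derived from the documents, and the assumed scale above should not be quoted as an estimate. The conclusion rests on reading the Discussion sentence as written and on at least some prescriptions being adjusted, which the article presents as a defining feature of the trial. It should be corrected because it is a stated rule that works against the blinding, not a detail left to a fuller document.

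**What to change.** Reconcile sections 3.3.2, 3.4 and 4. Replace the Discussion sentence with a statement along these lines: whenever the individualized prescription is modified, the control is re-matched to the current prescription according to the specification in section 3.3.2, and the pharmacist prepares both products so that neither patient nor physician can infer the period from whether a change appears.

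Section 3.4 should say the same and should describe, consistently with it, how modifications arising during a placebo period are handled. When and how a prescription is modified remains for the investigators to settle.

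Optionally, record a treatment guess at the end of each cycle, so that the success of blinding can be examined.

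The cost is extra pharmacy preparation at each modification, in a trial where the pharmacist already prepares both products for each patient, and one added question per cycle if the guess is collected.
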